### Outcome measures at the primary endpoint

#### Primary outcome

The primary endpoint of the trial is 52 weeks after baseline assessment. Assessments will also occur at 13, 26 and 39 weeks after baseline.

The primary outcome is the number of days spent in mainstream education and/or employment since baseline. Because some study participants might engage in both education and employment during the course of the intervention, the number of days spent in each of education and employment will be separately recorded. To capture these data as accurately as possible, participants will receive the following two text-messages each week:
‘Orygen research. Think about the past 7 days, not including today. On how many days did you attend work or employment for which you were paid?’‘Orygen research. Think about the past 7 days, not including today. On how many days did you attend secondary school, education or training, working towards a qualification (for example VCE, VCAL, Certificate, Diploma, Degree, etc)?’

Participants will reply to each message with a number only (0–7). In order to compensate for any missed messages/non-responses, participants will be asked at each research assessment how many days they have attended education/employment in the past 13 weeks. The mean, minimum and maximum of the total numbers from the text-messages and the research assessments will all be considered in the analysis.

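### The back-up recall for the primary outcome looks back a fixed 13 weeks from each visit, so the weeks before a missed interim visit are not recovered at the next one

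*Protocol article*

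**What the plan says.** All of this is in the protocol article, under Primary outcome. The outcome is a running count: "The primary outcome is the number of days spent in mainstream education and/or employment since baseline". It is read at one time, since "The primary endpoint of the trial is 52 weeks after baseline assessment", and the interim visits are equally spaced: "Assessments will also occur at 13, 26 and 39 weeks after baseline".

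The main capture is by phone: "participants will receive the following two text-messages each week", one on paid work and one on education. The interview question is the back-up. Its stated purpose is "In order to compensate for any missed messages/non-responses", and its content is that "participants will be asked at each research assessment how many days they have attended education/employment in the past 13 weeks".

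The interview totals also enter the analysis in their own right: "The mean, minimum and maximum of the total numbers from the text-messages and the research assessments will all be considered in the analysis".

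Under Statistical methods, the main analysis is a t test on this outcome, and multiple imputation is an option if missingness turns out to be more than trivial.

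**The concern.** The outcome runs over a period fixed at both ends, from baseline to week 52. The recall window is fixed in length and tied to the day of the visit. It is not tied to baseline, to the last completed assessment or to the week-52 date. The two agree only when every visit is held and held on time.

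What is at stake is the completeness of the primary outcome in participants who miss visits. The recall exists to fill weeks with no text reply. If it does not reach back over a missed visit, it fails in the situation for which a back-up is most useful. Attendance that was never asked about cannot be recovered at the analysis stage; it can only be imputed.

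**Working it through.** **Inputs.** From Primary outcome: follow-up 0 to 52 weeks; visits nominally at 13, 26, 39 and 52 weeks; look-back of 13 weeks at each. The shifts of 2 and 4 weeks used below are assumptions for illustration, because the article gives no visit window.

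**Rule.** A visit held at week v covers weeks v − 13 to v. For each pattern, count the weeks of 0–52 that are not covered, those covered twice, and those counted but outside 0–52.

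**The schedule as planned, then departures from it.**

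| Visits held (week) | Window that changes | Not covered | Counted twice | Outside 0–52 | Weeks summed |
|---|---|---|---|---|---|
| 13, 26, 39, 52 | none | 0 | 0 | 0 | 4 × 13 = 52 |
| 13, 39, 52 | 13–26 never asked | 13 (13–26) | 0 | 0 | 3 × 13 = 39 |
| 15, 26, 39, 52 | 2–15 | 2 (0–2) | 2 (13–15) | 0 | 52 |
| 13, 24, 39, 52 | 11–24 | 2 (24–26) | 2 (11–13) | 0 | 52 |
| 11, 26, 39, 52 | −2 to 11 | 2 (11–13) | 0 | 2 (before baseline) | 52 |
| 13, 26, 39, 56 | 43–56 | 4 (39–43) | 0 | 4 (after week 52) | 52 |
| 15, 28, 41, 54 | all four shift | 2 (0–2) | 0 | 2 (after week 52) | 52 |

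**Missed interim visit.** The gap is 13 / 52 = 25% of follow-up. Because the texts are the main source, the days actually lost for that participant are

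days lost = r × u,

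where u is the number of those 13 weeks with no text reply (0 to 13) and r is days attended per week. With r assumed to be 3, the loss runs from 3 × 0 = 0 days if every text was answered to 3 × 13 = 39 days if none was.

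**Off-schedule visits, all four held.** The windows always sum to 52 weeks, so

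weeks not covered = weeks counted twice + weeks outside the period.

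Every row of the table with four visits satisfies this. If k weeks are displaced, the error in the participant's total is

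k × (weekly attendance in the substituted weeks − weekly attendance in the omitted weeks).

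This is zero at a steady attendance rate. A difference of one day a week with k = 4 would give 4 × 1 = 4 days. The three columns must therefore not be added up as if each were a separate error.

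**The same patterns with a question anchored to the last completed assessment and stopped at week 52.**
- Week-26 visit missed: 0–13, 13–39, 39–52, so 13 + 26 + 13 = 52.
- First visit at week 15: 15 + 11 + 13 + 13 = 52.
- Final visit at week 56: the last window is 39–52, so 13 + 13 + 13 + 13 = 52.
- Final visit at week 50: 13 + 13 + 13 + 11 = 50, leaving 2 weeks uncovered.
- Final visit missed: 3 × 13 = 39, leaving 13 weeks uncovered, as under the present description.

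**The case against.** Several points on the other side have weight.

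- *The interview item is described, not quoted.* The two texts are given word for word, but the recall question is paraphrased. With visits 13 weeks apart, the phrase may be shorthand for the time since the last visit, and the interview form may already use dates. This stands as a limit on certainty. The article nevertheless states a look-back of fixed length, and nothing else in it corrects this.
- *Visit windows and rules for missed visits belong to the full protocol.* Agreed, and their absence is not the point. No window makes a 13-week look-back reach over a missed visit.
- *The recall is only the back-up.* Agreed: a week outside it is lost only if the text for that week was also unanswered. Enrolment, randomisation and retention also describes a tracking database and assessments at home or in the community, which should limit missed visits. That people who miss visits also miss texts is plausible but not documented.
- *A missed visit is an ordinary missing-data problem.* Partly so. Imputation may be considered, but these weeks could be asked about at the next visit at little cost, which is better than imputing them. Nor would imputation remove days counted twice or after week 52, which look like observed data.

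A reader might infer that late visits alone seriously distort the outcome. The working does not support that: with all four visits held, omitted and substituted weeks balance in number and only the difference in attendance between them remains. A reader might also infer a fault in the weekly text, which asks about "Think about the past 7 days, not including today". A seven-day question sent weekly covers the period without gaps if answered the same day, and the article gives no late-reply rate. That point is too slight to act on.

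**Conclusion.** The point holds in a limited form. Followed as described, the recall covers baseline to week 52 exactly only if all four visits are held on schedule. The main fault is the missed interim visit: 13 weeks, or 25% of follow-up, are not recalled at the next visit, and those of them without a text reply are lost. The lesser fault is the off-schedule visit, where the error is a difference in attendance between displaced weeks and is usually small.

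It is tempting to go on to say that the comparison of IPS with UVS is biased by some number of days. The article does not support a figure. It gives neither visit adherence nor text response, overall or by arm, and any such figure would also have to assume how partly covered totals are scored. The conclusion rests on reading the description of the recall literally. The change is still worth making, because it is cheap and the missing information cannot be collected afterwards.

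**What to change.** At each assessment, ask about days attended since the date of the last completed assessment, or since baseline if there has been none, and read that start date out to the participant. At the final visit, stop the count at day 364 after baseline (52 × 7), whenever the visit takes place. The weekly text needs no change.

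The cost is one change to the interview question and two date fields in the database. Trial status says that recruitment is under way, so the change would go to the ethics committee as Study design describes. For assessments already held, the visit dates show which weeks each answer covered.

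There are two drawbacks. After a missed visit the recall period exceeds 13 weeks (26 weeks after one missed interim visit) and is less exact. A missed or early final visit still leaves a gap, which must be handled as missing data.

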#### Secondary outcomes

Cost-effectiveness of IPS compared with UVS. Intervention costs will be determined using study budgetary information, as well as the client contact information maintained by IPS practitioners. Other costs will be measured using a Resource Use Questionnaire (RUQ) adapted for use in this study. This questionnaire includes information on primary and specialist health and mental health care, hospitalisation, pharmaceuticals and other health and non-health sector services (such as accommodation), as well as other non-health sector resource use, such as other vocational services. Medicare (MBS) and the Pharmaceutical Benefits Scheme (PBS) administrative data will also be requested for participants who consent to the collection of these data. Welfare benefits as a primary source of income, and new commencements on welfare benefits, will be measured at each time pointQuality of life, as measured by the AQoL-8D (Assessment of Quality of Life) [56]. This 35-item self-report questionnaire assesses for quality of life across eight dimensions: Independent living, Pain, Senses, Mental Health, Happiness, Coping, Relationships, Self-worth. It can also be used to determine quality-adjusted life years (QALYs) for economic analysis of the interventionBPD severity, as measured by BPDSI-IV (Borderline Personality Disorder Severity Index) [57]. This 70-item semi-structured interview is based upon the SCID-II BPD module. It assesses current frequency and severity of each *DSM-IV* BPD criterion

### Additional measures

#### Interview/researcher rated

The SCID 5-RV (Structured Clinical Interview for *DSM-5* Research Version) [58] will be used to assess for mental-state pathology and for syndromal diagnosesThe SCID 5-PD (Structured Clinical Interview for *DSM-5* Personality Disorders) [58] will be used to assess for personality disorder pathology and for syndromal diagnosesThe SOFAS (Social and Occupational Functioning Assessment Scale) [59] is a single-item scale (1–100) used to rate social and occupational functioning

### Data management

Trial data will be safely stored in password-protected computer databases, accessible only by members of the research team. Paper copies of participant files will be stored in locked filing cabinets in a swipe access storage area, co-located in a monitored building with research personnel. All participant files will be de-identified, with each participant allocated a unique identification number. Personally identifiable material, such as study consent forms, will be stored separately from research data files. This is fully explained in the participant informed consent form.

Data integrity will be supported by a range of means. The trial database is programmed to have range checks for data values, minimising the chance of data being recorded incorrectly. Data verification, through double data entry, will be undertaken on a random sample of 30 cases at baseline, with an a priori acceptable data-entry error rate set at 0.5%. More data-checking will be conducted if the error rate is above 0.5%. Data monitoring will be undertaken by the trial sponsor for the duration of the study. The monitor will be available to advise and assist with issues relating to study progress, protocol, regulatory and ethical adherence, and data accuracy.

### Statistical methods

Study sample size and power calculation are based on comparing groups in terms of the primary outcome measure. A sample size of 54 per group (*N* = 108) should detect an effect size of 0.62 with 80% power and a 5% significance level. This allows for a 14% dropout rate, based upon two previous RCTs conducted in the same population and setting [66, 67].

The main intent-to-treat data analysis will employ a *t* test to compare the two intervention groups in terms of the primary outcome measure. As a secondary analysis, the randomisation stratification variables of age and gender will be used as covariates and the two intervention groups will be compared using the general linear model. Other covariates, such as educational level and employment history, will also be considered. Logistic regression and general linear model analysis will be employed to analyse the secondary outcome measures, depending upon the nature of the measures. Multiple imputation will be considered if the amount of missing values is non-trivial.

The cost-effectiveness of IPS, compared with UVS, will be determined by a cost-consequences analysis comparing the intervention with comparator, with the full spectrum of differences in outcomes included in the study.

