**Methods/design:**

INVEST is a single-blind, parallel-groups, randomised controlled trial (RCT). The randomisation is stratified by gender and age and uses random permuted blocks. The interventions are 39 weeks of either IPS, or ‘usual vocational services’ (UVS). Participants will comprise 108 help-seeking young people (aged 15–25 years) with three or more *DSM-5* BPD features and a desire to study or work, recruited from the Helping Young People Early (HYPE) early intervention programme for BPD at Orygen, in Melbourne, Australia. All participants will receive the HYPE intervention. After baseline assessment, staff who are blind to the intervention group allocation will conduct assessments at 13, 26, 39 and 52 weeks. At the 52-week primary endpoint, the primary outcome is the number of days in mainstream education/employment since baseline. Secondary outcomes include the cost-effectiveness of the intervention, quality of life, and BPD severity.

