### Enrolment, randomisation and retention

Interested participants will complete the informed consent process with a member of the research team. This involves full written and verbal presentations of the study information, with all participants providing written, informed consent prior to commencement of formal study screening and eligibility confirmation. For potential participants aged under 18 years, a parent or legal guardian will be included in each stage of this process. Details of complaints and compensation procedures, and contact information for research personnel are included in the participant informed consent form. In addition to study consent, participants will be asked if they consent to their data being used for future research, and if they consent to being contacted for future research opportunities. Participants can opt in or out of one or both of these and still participate in INVEST.

Once eligibility for the trial is confirmed, the trial coordinator will randomly and consecutively assign participants to receive 39 weeks of either IPS or UVS, in a ratio of 1:1, using a password-protected computer programme, with a randomisation sequence that is computer-generated. Randomisation uses permuted blocks and is stratified by gender (female/not female) and age (< 18 years/18–25 years).

A graduate research assistant (RA) will conduct initial screening and will determine eligibility (in consultation with the study coordinator and principal investigator). The RA will also conduct all research assessments at 13, 26, 39 and 52 weeks. Intervention group assignment will be concealed from the RA (single-blind) conducting the assessments and from the biostatistician conducting the primary analyses. Blinding of the RA will be achieved and maintained by frequently reminding clinicians of the importance of the blind, excluding the RA from all clinical discussions, and forbidding the RA from accessing participants’ medical records. Any cases of un-blinding will be documented and another ‘blind’ RA will conduct assessments thereafter. Blinding of the RAs will be tested at the end of their employment or the end of the study, using an online self-report instrument designed specifically for the study. Study investigators will not be blind to group allocation, and the nature of the intervention precludes concealment from participants or clinicians.

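### The sample-size figures do not reproduce: 0.62 SD at 80% power with 14% dropout needs 49 per arm, not 54, and the mismatch is conservative

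*Protocol article*

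**What the plan says.** The sample-size statement is in the protocol article under Statistical methods. "A sample size of 54 per group" (N = 108) "should detect an effect size of 0.62 with 80% power and a 5% significance level". The next sentence gives the attrition allowance and its source: "This allows for a 14% dropout rate, based upon two previous RCTs conducted in the same population and setting".

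The same section names the primary analysis: "The main intent-to-treat data analysis will employ a *t* test". Covariate adjustment for the stratification factors is kept for a secondary analysis. Under Enrolment, randomisation and retention, allocation is "in a ratio of 1:1". The abstract gives the same total of 108.

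The article does not say whether the 5% level is one-sided or two-sided. It states no design effect, rank-test allowance or other inflation beyond the 14%.

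**The concern.** Apart from sidedness, the paragraph supplies everything needed to repeat the calculation: test, allocation, effect size, power, significance level, dropout and N. When it is repeated, the result is not 54 per arm. At least one of the detectable effect, the power and the dropout allowance is then not the figure that produced N, or some further allowance was made and not stated.

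This paragraph is the article's only justification of N. Readers will use 0.62 as the effect the trial was built to detect, above all if the result is null. They will use 14% as the planned attrition, which the article presents as drawn from earlier trials. As written, they cannot tell which figure to rely on.

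**Working it through.** **Inputs (protocol article).** 54 per arm, effect size d = 0.62, power 80%, significance level 5%, dropout 14%, unadjusted t test (all Statistical methods); 1:1 allocation (Enrolment, randomisation and retention). *Assumption:* two-sided test.

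**1. Attempt to reproduce 54 per arm.**

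Normal approximation: n = 2(z₀.₉₇₅ + z₀.₈₀)² / d² = 2(1.960 + 0.842)² / 0.62² = 40.8, so 41 per arm.

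Noncentral t: n = 41.8, so 42 per arm analysed (power at 42 is 80.2%).

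Inflated for dropout: 42 / (1 − 0.14) = 48.8, so 49 enrolled per arm, N = 98. The article has 54 and 108, a difference of 5 per arm and 10 in total.

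**2. From 54 per arm forwards.**

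54 × 0.86 = 46.4, so 46 to 47 analysed per arm.

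| Analysed per arm | Effect detectable at 80% power | Power for 0.62 |
|---|---|---|
| 42 | 0.619 | 80.2% |
| 46 | 0.590 | 83.7% |
| 47 | 0.584 | 84.5% |
| 54 (no dropout) | 0.544 | 89.1% |

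**3. Dropout at which 54 per arm just gives 80% power for 0.62.**

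1 − 42/54 = 12/54 = 22.2% (22.6% with the unrounded 41.8).

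**4. Other readings of the same inputs.**

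| Reading | Result |
|---|---|
| Normal approximation, 14% dropout | 41 analysed, 48 enrolled per arm |
| Dropout applied as n × 1.14 | 42 × 1.14 = 47.9, so 48 per arm (47 with the normal approximation) |
| 54 taken as completers | 89% power for 0.62; 80% power for 0.54 |
| One-sided 5% | 33 analysed, 39 enrolled per arm |
| 85% power | 48 analysed, 56 enrolled per arm |
| 90% power | 56 analysed per arm before any dropout |
| Rank-test efficiency 0.955 | 41.8 / 0.955 = 43.8, so 44 analysed; 44 / 0.86 = 51.2, so 52 enrolled per arm |

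None returns 54. Applying the 14% twice comes close (42 × 1.28 = 53.8; 42 × 1.14² = 54.6). Nothing in the article suggests that this was done, and it would not be a valid dropout allowance.

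**The case against.** Four points can be made for the text as it stands.

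*The figures can be read as sufficient rather than exact.* The article does not say that 54 is the minimum, that 0.62 is the smallest detectable effect, or that power is exactly 80%. After 14% dropout about 46 per arm remain and 42 are needed, so on that reading every figure holds. This stands against the stronger claim, which a reader might infer, that the four figures contradict one another. It does not make the paragraph reproducible. A statement of N, effect, power and dropout is normally taken as one calculation, and on that usual reading the figures do not agree.

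*The error is harmless in direction.* This stands. With 14% dropout the trial has about 84% power where 80% is stated, and about four analysable participants per arm to spare (46 against 42). A reader who sees a sample-size mismatch might conclude that the trial is underpowered; these inputs show the opposite.

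*The full protocol may hold an allowance that the article left out.* This cannot be excluded. The outcome is a bounded count of days, and a planner might add a margin for that. A rank-test efficiency of 0.955 narrows the gap to 52 per arm without closing it. A lower efficiency, about 0.90 (41.8 / 46.4), would close it. But the article names a t test and states no such margin, so the published figures remain unexplained. The point is not that detail is missing, but that the figures given do not yield the N given.

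*Two-sided testing is assumed.* This is correct: the article gives only the 5% level. The alternative widens the gap (39 per arm against 54), so the assumption favours the article.

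**Conclusion.** The point holds as a reporting error of modest size. For a two-sided 5% t test with 1:1 allocation, the stated effect, power and dropout lead to 49 per arm (N = 98), not 54 (N = 108). The stated N and dropout lead to a detectable effect of about 0.59 SD rather than 0.62, or about 84% power rather than 80%. The gap of five per arm is too large for rounding or for the choice between normal and t formulas. The planned test, the type I error and the recruitment target are not affected.

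A reader might also infer that the trial really planned for dropout of 22% or more and published too low a figure. The documents do not support that. The 22% is only what results from solving the equation backwards; the article mentions no dropout figure other than 14%, and it ties that figure to two earlier trials. The calculation shows that the figures do not fit together, not which of them was entered differently.

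**What to change.** Keep N = 108 and replace the power statement with one that reproduces, for example:

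*54 participants per arm, about 46 per arm after 14% dropout, give 80% power for a difference of 0.59 SD (84% for 0.62 SD) in a two-sided t test at the 5% level.*

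It would help to add that 80% power for 0.62 SD is kept up to about 22% dropout.

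If a different dropout rate was used to reach 54, correct the 14%. If a further allowance was used, state what it is and how large. In either case state the sidedness of the test.

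The cost is one sentence. Recruitment, analysis and budget are unchanged.

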## Background

Borderline personality disorder (BPD) is a severe mental disorder that is characterised by difficulty managing interpersonal relationships, an unstable sense of self, intense and volatile emotions and impulsive behaviours [1]. The clinical onset of BPD usually occurs between puberty and young adulthood (‘young people’; aged 12–25 years) [2]. From this age, BPD is associated with substantial and enduring impairments in social and occupational functioning [3–6]. While these impairments are associated with characteristics of BPD, such as impulsivity [7], prospective studies have consistently found that functional impairment persists long after the diagnostic features of the disorder have attenuated [8–11].

BPD in young people predicts the persistence of functional impairments into adulthood [5, 6]. The severity of BPD features at age 14 is associated with lower academic and occupational attainment 20 years later [6]. Personality disorder severity at age 24 years is associated with the absence of post-school qualifications, receipt of disability welfare payments, and relationship difficulties at age 35 years [5]. Young people, aged 15–18 years, who experience severe mental illness, including BPD, are three times more likely to be disengaged from education than their peers in the general population [12]. Failure to begin tertiary education is associated with being not in education, employment or training (NEET) among 19–25 year olds [13] and, in one study of young people at entry into a specialist BPD treatment programme, 62% were either partially or fully NEET [14].

The enduring effects of early vocational disruption in this group are evident, with BPD more strongly associated with unemployment and impairment at work than depression or anxiety [15]. BPD features are consistently linked with impaired work performance, with even the presence of subthreshold features (1–4 *Diagnostic and Statistical Manual of Mental Disorders, version 5* (*DSM-5*) criteria) being associated with impaired work performance in a population sample of 18–64 year-olds [16].

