#### Inclusion criteria

Young people (all genders) aged 15–25 years inclusiveThree or more BPD features, assessed by the Structured Clinical Interview for *DSM-5* Personality Disorders (SCID 5-PD)A desire to enter mainstream education and/or employment (in which they are not currently engaged)Ability to give informed consent and adhere to study protocolSufficient fluency in English

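### Randomisation is stratified by gender and age, but the main analysis is an unadjusted t test; the model that matches the design is only secondary

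*Protocol article*

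**What the plan says.** The section on enrolment and randomisation states: "Randomisation uses permuted blocks and is stratified by gender (female/not female) and age", with age split at 18 years. Allocation is "in a ratio of 1:1, using a password-protected computer programme".

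Under Statistical methods, the primary comparison is fixed: "The main intent-to-treat data analysis will employ a *t* test to compare the two intervention groups in terms of the primary outcome measure". The stratifiers come in one step down: "As a secondary analysis, the randomisation stratification variables of age and gender will be used as covariates", in a general linear model. The next sentence adds: "Other covariates, such as educational level and employment history, will also be considered".

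The inclusion criteria ask for "A desire to enter mainstream education and/or employment (in which they are not currently engaged" (a parenthesis in the original). The primary outcome counts all days in mainstream education and/or employment from baseline to week 52.

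**The concern.** Stratified randomisation makes the arms more alike on the stratifiers than simple randomisation would, so the treatment estimate varies less. An unadjusted t test does not use this. Its standard error still contains the between-stratum variation that the design has removed from the comparison. If the strata predict the outcome, the test is conservative and loses power.

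Age is a plausible predictor here. Participants under 18 can still be of school age, and the school-based support described under UVS is for ages 15 to 18.

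Prior vocational situation may also predict days attended. The inclusion criterion can be read to admit someone engaged in one domain who wants to enter the other, such as a pupil who wants a job. That person's existing days would count from the start. No baseline measure of this is committed to as a covariate in the main analysis.

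What is at stake is precision: a somewhat wider confidence interval and a few points of power.

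**Working it through.** **Inputs.** From Statistical methods: 54 per group, standardised effect 0.62, 80% power, 5% significance level (taken as two-sided, since the article does not say), 14% dropout. Analysed per arm: 54 × 0.86 = 46.4, taken as 46. R² is the share of outcome variance that a covariate explains. The documents give none, so a range is assumed.

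**The plan's own figure.** An exact two-sample t calculation at 0.62 needs 41.8, so 42, per arm. Then 42 / 0.86 = 48.8, so 49 per arm or 98 in total, against the stated 108. The stated figure is not reproduced, but the gap is on the safe side and does not bear on this point. With 46 per arm, unadjusted power at 0.62 is 83.7%, and 80% power is reached at an effect of 0.590.

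**Type I error of the unadjusted test under stratified randomisation.** For strata explaining R², the large-sample level is 2 × [1 − Φ(1.96 / √(1 − R²))].

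| Strata R² | 1.96 / √(1 − R²) | Actual level |
|---|---|---|
| 0.02 | 1.980 | 4.8% |
| 0.05 | 2.011 | 4.4% |
| 0.10 | 2.066 | 3.9% |

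The level is at or below 5%, never above.

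**Gain from adjusting for the strata (normal approximation).** The expected test statistic is λ = 0.62 × √(46/2) = 2.973. Stratification has already lowered the true variability of the unadjusted estimate, so its power is Φ((λ − 1.96) / √(1 − R²)). Adjusted power is Φ(λ / √(1 − R²) − 1.96).

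| Strata R² | Unadjusted | Adjusted | Gain (points) |
|---|---|---|---|
| 0 | 84.5% | 84.5% | 0 |
| 0.05 | 85.1% | 86.2% | 1.1 |
| 0.10 | 85.7% | 88.0% | 2.3 |

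**Simulation.** Each scenario had 4,000 replicates of 108 participants in four strata. Assumptions: blocks of 4, 80% female, 35% under 18, strata acting through age, normal outcome, 14% random dropout. Adjusting for age and gender changed power at 0.62 by:

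- −0.2 to −0.4 points at strata R² = 0
- +0.9 to +1.9 points at 0.05
- +2.2 to +2.8 points at 0.10

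The simulated type I error of the t test ran from 3.85% to 5.15% over nine scenarios. The Monte Carlo standard error is √(0.05 × 0.95 / 4000) = 0.34 points, so there is no sign of inflation.

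**Gain from one further baseline covariate.** This covariate is not balanced by design, so its full R² is available. By formula (residual SD × √(1 − R²), exact t, 46 per arm):

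| Covariate R² | Power at 0.62 | Effect detectable at 80% power |
|---|---|---|
| 0 | 83.7% | 0.590 |
| 0.05 | 85.5% | 0.576 |
| 0.10 | 87.3% | 0.560 |
| 0.25 | 92.5% | 0.511 |

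In the simulation, adding such a covariate to the age- and gender-adjusted model gave:

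- 2.6 to 3.4 points at R² = 0.10 (for example 85.7% to 88.9%)
- 7.8 to 8.2 points at R² = 0.25 (for example 83.9% to 92.0%)

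**The case against.** The best defence is that an unadjusted t test is simple, valid and leaves no choice of covariates. The adjusted model is already planned as secondary, and power at the design effect exceeds the 80% target without adjustment. All of that stands, and it limits the point to efficiency.

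A reader might infer more than the documents support:

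- **That baseline engagement is the strongest predictor.** No section says so or reports any association with days attended. The inclusion criterion restricts this variable and can equally be read as excluding anyone engaged in either domain. The Background figure, "62% were either partially or fully NEET", describes entrants to a specialist programme in a cited study, not people who passed this trial's eligibility check.
- **That chance imbalance is left uncorrected or biases the result.** Stratified blocks limit imbalance in age and gender, and the secondary model adjusts for both. Chance imbalance in other variables is ordinary sampling variation, which the t test's standard error covers.
- **That covariates could be picked after the fact in the confirmatory test.** The sentence on other covariates follows the one on the secondary analysis. The t test has no covariates, and the final list for the secondary model may be in an analysis plan that is not shown.
- **That power would rise by 10 points or more.** This needs an R² of 20 to 30%, for which the documents give no basis, or a true effect below the design value.
- **That AQoL-8D and BPDSI-IV will be analysed without their baseline values.** The article names the general linear model for such outcomes and does not rule baseline values out.

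**Conclusion.** The point holds as a modest one. The article fixes a main analysis that does not match its own randomisation and places the matching model second. The consequence is a slightly conservative test and some lost precision; validity is not affected.

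For age and gender alone the loss is about 0 to 3 points of power for R² up to 0.10. One further prognostic covariate is worth about 3 points at R² = 0.10 and about 8 at R² = 0.25. These sizes rest on the assumed R² values, a true effect of 0.62, about 46 analysed per arm, a two-sided 5% level and an approximately normal outcome. If the covariates explain almost nothing, the gain is nil and the cost is a fraction of a point.

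**What to change.** Swap the two analyses. Make the primary analysis a linear model of days in education or employment on arm, gender stratum and age stratum, and report the unadjusted t test as a sensitivity analysis.

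Name in advance one further baseline covariate that is already collected. Engagement status at screening is one candidate, since it is needed to judge eligibility. Educational level or employment history, which the article already mentions, is the other. A count of days attended before baseline is less suitable, because Table 1 lists no such measure at baseline and recruitment began in October 2019.

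Record the change, with its date, before anyone sees outcome data by arm. It needs no extra participants or visits, only new wording and slightly more analysis work.
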